### Statistical analyses

In non-randomised comparative studies, variations in case mix between centres can influence the interpretation of outcome data [48]. Therefore, for each of the data sets collected at T1 through T4, differences in outcome variable between the 2 services will be tested using multiple MANCOVA's, entering various indicators of case mix as co-variates, i.e. age, gender, ISS, number of complications, pre-trauma psycho-social status.

When patients drop out of the study, the reason for their withdrawal will be recorded. Drop-outs may bias the treatment effect evaluations. Therefore, the following regime will be applied:

- Missing T4 measurement: 'last-observation-carried-forward' principle will be applied.

- Missing T3 or T2 measurement: linear interpolation of data using data from adjacent time points (e.g. T1 and T4) for imputation.

- Missing T0 or T1 measurement or more than 2 missing measurements: discarding of patient data and influx of additional patient in order to meet n = 82 per group.

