To date, no exact data on differences in quality of life outcome between different treatment services for multi-trauma patients are available. Czyrny and co-workers [14] report an improvement in motor FIM score of 30.2 in a small group of bilateral lower limb multi trauma patients having received both hospital and subsequent rehabilitation treatment, at a mean length of stay of 62.8 (+/-6.0) days. In order to detect a difference of 15% of such improvement in FIM score between SFTRS and CTCS at T1 (assuming a two-sided significance level of 0.05, a power of 80%, and a common standard deviation (sd) of 9.5 as reported by Czyrny [14]), 71 persons per group are needed. Taking into account a 15% loss to follow-up, the required sample size is 82 persons per group (164 persons in total).

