### Demographic and medical variables

Upon arrival at the A&E (= T0) the following variables will be recorded: age, gender, medical history, mediation usage, diagnosis, ISS score, date and time of trauma and Glasgow Coma Scale (GCS).

As soon as possible post-injury the following data are collected: trauma treatment, possible complications (description, number and extend) and time in hospital. The following additional data are recorded upon admission in the rehabilitation centre: individual rehabilitation treatment aims, pre-trauma psychosocial status and pre-trauma employment status.

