## Discussion

The main objective of this study is to examine the effectiveness, the costs and the cost-effectiveness of an integrated Supported 'Fast Track' Rehabilitation Service for multi-trauma patients (SFTRS) involving dedicated early rehabilitation intervention programs.

As there are no publications found about contrasts in (cost-) effectiveness between different multi-trauma rehabilitation services it is important to investigate whether a new rehabilitation service is more effective than the conventional service.

During the conceptualisation of the study design several choices had to be made. The major ones will be discussed.

First, randomisation in this study is not possible because of practical and ethical reasons. The distance between the two centres is approximately 150 km. Since this study includes acute (complex) multi-trauma patients who need to be take care of as soon as possible it is not justified to transport patients for hours to accommodate to any randomisation procedure.

Second, in literature the 'severe multi-trauma' patients are frequently reported as having at least 2 or more injuries of which at least 1 is life threatening (ISS > = 16). However, during a pilot study it became apparent that part of the multi-trauma patients suffering from complex multiple injuries and who were admitted to the rehabilitation centre had an ISS < 16. Clinically speaking, it concerned patients suffering from one of the following injuries: a) complex multiple injuries on both lower extremities; b) a combination of one upper and one lower extremity injury, the latter of which could not be used in load-bearing; or c) complex pelvis/acetabulum fractures. Multi-trauma patients, who often suffer from skull and brain injuries, generally have an ISS > = 16. However, especially in complex pathology of the locomotor system, necessitating intensive rehabilitation training, the AIS system often scores less. Given the fact that these patients do participate in CTCS and SFTRS, indicating that they do belong to the target population in accordance with the other inclusion criteria, these patients have been added to the project population. This classification of multi-trauma patients is in accordance with the revised AIS coding ("AIS upgrading") which is currently being elaborated internationally.

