In the present study the definition of multi-trauma reads: "Multi-trauma is defined as having at least 2 or more injuries of which at least 1 is life threatening, including a) trauma with ISS > = 16, b) complex multiple injuries on both lower extremities, c) a combination of one upper and one lower extremity injury, the latter of which can not be used in load-bearing, or d) complex pelvis/acetabulum fractures".

In conclusion, this paper describes the design of a prospective, multi-centre, non-randomised clinical trial that will investigate the (cost-) effectiveness of a new Supported Fast Track multi-Trauma Rehabilitation Service (SFTRS). The inclusion of the patients will start in October 2008 and will continue until May 2010. The results of this study will give evidence whether the new 'fast track' rehabilitation service for multi-trauma patients is more effective than the conventional care service, and thus should be introduced nation-wide.

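### The closed covariate list leaves out GCS, injury type and baseline FIM, and relies on ISS for admission severity, so avoidable case-mix confounding can remain in a non-randomised contrast

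*Protocol article*

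**What the plan says.** Patients are allocated by region, without randomisation: SFTRS patients come from the area of one trauma centre and the reference group from that of another (Population). The Statistical analyses section names the resulting threat: "In non-randomised comparative studies, variations in case mix between centres can influence the interpretation of outcome data". Its remedy is a set of MANCOVAs on the T1 to T4 data, "entering various indicators of case mix as co-variates, i.e. age, gender, ISS, number of complications, pre-trauma psycho-social status".

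Other sections bear on that list:

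- **Demographic and medical variables:** the items recorded on arrival include diagnosis and "ISS score, date and time of trauma and Glasgow Coma Scale (GCS").
- **Abstract and Data collection:** both schedule a baseline measurement. The missing-data rules in Statistical analyses discard a patient whose T0 is missing.
- **Population (sample size):** "In order to detect a difference of 15% of such improvement in FIM score between SFTRS and CTCS at T1". The target is thus derived from an improvement in FIM.
- **Discussion:** some pilot patients with complex limb or pelvic injuries had ISS below 16 and were added to the population. Patients with skull and brain injuries generally reach 16 or more. The stated reason is that "especially in complex pathology of the locomotor system, necessitating intensive rehabilitation training, the AIS system often scores less".

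**The concern.** With no randomisation, covariate adjustment is the only protection against case-mix differences that the article states. Its list is introduced by i.e., which closes it, so this is not a detail left open for a later document.

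The list carries injury severity at admission through ISS alone. By the Discussion's own account, ISS partly reflects the type of injury. Complex locomotor injury that needs intensive rehabilitation can score low, and brain injury generally scores high. Patients with the same ISS may therefore have different injuries and a different outlook on FIM. If the two regions differ in their mix of head and limb or pelvic injury, adjusting for ISS will not remove that difference. GCS and diagnosis would help, and both are already collected.

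Baseline FIM raises a similar question. The target effect comes from a FIM improvement, and a missing T0 costs a patient their place in the analysis, yet no T0 value enters the model. At stake is whether a difference at T1 to T4 can be attributed to the service.

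**Working it through.** **1. The plan's own figure.** Inputs from Population: FIM improvement 30.2, target 15% of it, SD 9.5, two-sided alpha 0.05, power 80%.

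- Target difference = 0.15 × 30.2 = 4.53 points (0.477 SD).
- n per group = 2 × [9.5 × (1.960 + 0.842) / 4.53]² = 69.04, so 70 by the normal formula. The t-test solution is 70.01, so 71. The stated 71 reproduces.
- 71 × 1.15 = 82, as stated. (71 / 0.85 gives 84; nothing here depends on that difference.)
- SE of the difference at 71 per group = 9.5 × √(2/71) = 1.594.

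**2. What is recorded against what is used.**

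| Item | Recorded? | In the model? |
|---|---|---|
| Age, gender, ISS | Yes, on arrival | Yes |
| GCS | Yes, on arrival | No |
| Diagnosis (gives injury type) | Yes, on arrival | No |
| FIM at T0 | Baseline visit scheduled; instrument not itemised | No |
| SF-36 at T0 | Unclear: Determination of costs places quality of life at T1 to T4 | No |

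**3. How large the bias could be.** The document gives no imbalance between regions and no T0–T1 correlation. The values below are assumptions. They stand for what remains after the five listed covariates.

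*Injury type or GCS group.* Bias = difference in proportion × effect in SD × 9.5.

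- Low: 0.10 × 0.5 × 9.5 = 0.475 points; 0.475 / 4.53 = 10%.
- High: 0.20 × 1.0 × 9.5 = 1.90 points; 1.90 / 4.53 = 42%.

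*T0 FIM.* Bias = imbalance in SD × r × 9.5, taking equal SDs at T0 and T1.

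- Low: 0.1 × 0.3 × 9.5 = 0.285 points; 0.285 / 4.53 = 6%.
- High: 0.3 × 0.7 × 9.5 = 1.995 points; 1.995 / 4.53 = 44%.

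*Two-sided error rate when the services do not differ* = 1 − Φ(1.96 − bias/1.594) + Φ(−1.96 − bias/1.594). This gives 6% to 22% for injury type or GCS, and 5% to 24% for T0 FIM.

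**4. Precision.** Adjusting for T0 FIM would also change power, but the size depends on what the SD of 9.5 describes, which the sample-size paragraph does not settle. Power at 71 per group without T0 adjustment is 81%.

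| r | 9.5 is the SD of a score: multiply by √(1 − r²) | 9.5 is the SD of improvement: multiply by √((1 + r)/2) |
|---|---|---|
| 0.3 | 85% | 94% |
| 0.5 | 91% | 91% |
| 0.7 | 98% | 87% |

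Power rises in every cell, but the trend with r reverses. No single gain should be quoted.

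**The case against.** **Availability of T0 scores.** The strongest objection is that no section explicitly schedules FIM at T0. The variables itemised on arrival include neither FIM nor SF-36, and quality of life is placed at T1 to T4. COPM rates aims set during rehabilitation, so it has no comparable score at injury. This stands. A reader might infer that every outcome has an unused T0 score, and the document does not support that. The point is firmest for GCS and injury type. For FIM it rests on the scheduled baseline measurement and the T0 exclusion rule.

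**Timing of T0.** SFTRS brings in the rehabilitation physician very early, while T0 has no fixed window. A late T0 may already reflect the service, and adjusting for it could remove part of the effect. This also stands and shapes the fix.

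**Overlapping categories.** Nothing stops a patient with ISS of 16 or more from also having a pelvic fracture, so a single four-level a–d factor is undefined. This stands.

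**From AIS to ISS.** The Discussion speaks of AIS scoring less. Applying this to ISS is an inference, but the same paragraph connects it with patients whose ISS was below 16.

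**Region and service.** A reader might go further and attach an inflated error rate to having one region per service. The document gives no between-centre correlation, it describes the study as multi-centre with conventional care in several centres, and the added covariates would not cure the problem. The article discloses why randomisation was not possible. The closing phrase "and thus should be introduced nation-wide" also belongs to a sentence about whether the new service is more effective, so it is not an unconditional claim. What remains is a limit on interpretation that should be stated.

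**Conclusion.** The point holds for the covariate list. The article names case mix as the threat and closes the list. It leaves out GCS and injury type, which arrival data can supply, and it leaves out baseline FIM. The single admission severity score is one whose scoring, by the article's own account, often runs low in part of the target population. The resulting confounding is avoidable in part and can bias the contrast.

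A reader might infer that the contrast is biased, or by how much. The document supports neither, because direction and size cannot be derived from it. The range of 0.3 to 2.0 FIM points (6% to 44% of the target) rests on assumed residual imbalances of 0.1 to 0.3 SD in T0 FIM with r of 0.3 to 0.7, or of 10 to 20 percentage points in injury type or GCS group with effects of 0.5 to 1.0 SD. Smaller residual imbalances would give proportionally less.

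**What to change.** 1. **Covariates.** Keep ISS. Add GCS (or head injury yes/no) and injury type to the prespecified list. Code injury type as non-exclusive indicators for categories b, c and d, or state a hierarchy, because a–d overlap.
2. **Baseline FIM.** Add T0 FIM, with days from injury to T0, to the FIM model where T0 is taken before the services diverge. Report results with and without it.
3. **Reconcile the T0 content.** The Abstract, Data collection, Demographic and medical variables, and Determination of costs should agree on whether FIM and SF-36 are measured at T0. Add T0 SF-36 to its model only if it is collected.
4. **Sensitivity analysis.** Run a propensity-weighted analysis on the pre-treatment covariates. Number of complications does not belong there, since the Introduction expects SFTRS to reduce secondary complications.
5. **Conclusion.** State beside the closing sentence of the Discussion that region effects cannot be separated from the service effect.

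**Cost.** GCS and injury type need no new data and use a few degrees of freedom. Ensuring that T0 FIM precedes the divergence of services affects data collection as well as wording. Adjusting for a late T0 could remove part of an early service effect, which is why both sets of results are needed.

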**Methods/design:**

The study population includes multi-trauma patients, admitted to one of the participating hospitals, with an Injury Severity Scale score > = 16, complex multiple injuries in several extremities or complex pelvic and/or acetabulum fractures. In a prospective cohort study CTCS and SFTRS will be contrasted. The inclusion period is 19 months. The duration of follow-up is 12 months, with measurements taken at baseline, and at 3,6,9 and 12 months post-injury.

Primary outcome measures are 'quality of life' (SF-36) and 'functional health status' (Functional Independence Measure). Secondary outcome measures are the Hospital Anxiety & Depression Scale, the Mini-Mental State Examination as an indicator of cognitive functioning, and the Canadian Occupational Performance Measure measuring the extent to which individual ADL treatment goals are met. Costs will be assessed using the PROductivity and DISease Questionnaire and a cost questionnaire.

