### Data collection

Baseline measurements will be administered as soon as possible post-injury (= T0). Further measurements will be taken at 3 months (= T1), 6 months (= T2), 9 months (= T3) and 12 months (= T4) post-trauma (see also flow chart, figure 1).

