### Primary outcome measures

In the current study the primary outcome measures are FIM, measuring quality of life and SF-36, measuring functional health status. In several studies it was found that in multi-trauma patients quality of life and functional recovery do not solely depend on injury severity and complications [6-9], but also on psychological and social factors (e.g. [5,17-20]) as well as the patient's cognitive status [21]. The Functional Independence Measure (FIM) is widely used in assessing functional health status in different groups of patients. Baldry-Currens [22,23] recommended using the FIM in assessing trauma outcome, the FIM correlating high with measures of injury severity and demonstrating clinical and statistical significance. Similarly, Hetherington and co-workers [24,25] reported that in rehabilitation services, the FIM is a useful, practical and simple methodology, providing a measure for assessing the original disability, its progress and residual limitations. The National Trauma Data Bank collects data on trauma centre performance throughout the USA. As to functional outcome assessment in trauma patients FIM data are used [26].

At an international and interdisciplinary consensus conference in 1999 about the assessment and application of quality of life (QoL) measures after multiple trauma, experts clinicians and methodologists agreed on the SF-36 as generic tools for QoL assessment across all trauma patients [27]. In the proposed study both generic QoL and utilities will be derived using the SF-36. An overall utility score for population based QoL can be obtained, which facilitates comparisons with other interventions, i.e. the social tariff of the SF-36 [28-33].

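### Two unranked primary outcomes are tested at each of four visits, but the sample size gives the full 5% and 80% power to FIM at T1 alone

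*Protocol article*

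**What the plan says.** The abstract (Methods/design) lists two primary outcomes: "Primary outcome measures are 'quality of life' (SF-36) and 'functional health status' (Functional Independence Measure"). Table 2 lists the same two, and neither place ranks one above the other.

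Under Data collection, "Further measurements will be taken at 3 months (= T1), 6 months (= T2), 9 months (= T3) and 12 months (= T4) post-trauma".

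Statistical analyses gives the comparison rule: "for each of the data sets collected at T1 through T4, differences in outcome variable between the 2 services will be tested using multiple" MANCOVAs, adjusted for case-mix covariates. It states no significance level. It does not say whether each MANCOVA holds one outcome or several, and it singles out no visit.

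The only significance level is in the sample-size paragraph under Population. That calculation concerns one comparison, FIM at T1, "assuming a two-sided significance level of 0.05, a power of 80%, and a common standard deviation (sd) of 9.5". The benchmark is a cited study said to "report an improvement in motor FIM score of 30.2 in a small group of bilateral lower limb multi trauma patients", and the target is 15% of that improvement. The result is 71 per group, or 82 after loss to follow-up. There is no power statement for SF-36 or for T2-T4.

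The Introduction states one general hypothesis, that the new service is more (cost-)effective. The Discussion ties nation-wide introduction to the outcome of the study. Neither says which outcome or visit settles the question.

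**The concern.** The study is sized for one test, while the analysis section describes several tests of equal standing. These two parts of the article do not fit together.

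If all the tests are run at 5% and the favourable one is used to support the general hypothesis, the study's false-positive rate is not the 5% on which the sample size rests. If alpha is shared among the tests, the stated 80% power no longer applies. In either case the outcome and visit that carry the conclusion could be chosen after the data are seen. That matters here because the comparison is non-randomised and is meant to inform national introduction of the service.

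**Working it through.** **1. Inputs from the article.** Two primary outcomes; four post-baseline visits; two-sided 0.05; power 80%; SD 9.5; benchmark improvement 30.2; target 15% of it; 71 per group.

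**2. The plan's own figure.** Difference = 0.15 × 30.2 = 4.53 points. Standardised difference = 4.53 / 9.5 = 0.477. Normal approximation: n = 2 × [(1.960 + 0.842) / 0.477]² = 69.04, so 70. The t-based calculation gives 70.01, so 71. The stated 71 reproduces, and 71 × 1.15 = 81.65 gives the stated 82. Power with 71 per group is 80.6% (t-based). All of it is spent on FIM at T1 at the full 5%.

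**3. Family-wise error if each test is at 5% and any one suffices.** For k independent tests the error is 1 − 0.95^k:
- k = 2 (both outcomes at one visit): 9.75%
- k = 4 (one omnibus MANCOVA per visit): 18.5%
- k = 8 (each outcome at each visit): 33.7%

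**4. Allowing for correlation.** The article gives no correlations, so these are assumptions: 0.5 to 0.9 between visits (exchangeable) and 0.3 to 0.5 between outcomes. The results come from multivariate-normal simulation under the null. An omnibus test is a two-degree-of-freedom chi-square test per visit.

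| Between-visit correlation | 8 single tests | 4 omnibus tests |
|---|---|---|
| 0.5 | 27-28% | 16% |
| 0.8 | 20-21% | 12% |
| 0.9 | about 17% | about 10% |

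**5. Splitting alpha instead, 71 per group.** Normal approximation: power = Φ(0.477 × √(71/2) − z), where 0.477 × √(71/2) = 2.84.
- alpha 0.05, z = 1.960: 81% (t-based 80.6%)
- alpha 0.025, z = 2.241: 73% (t-based 72%)
- alpha 0.05/8 = 0.00625, z = 2.734: 54% (t-based 53%)

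Restoring 80% power would need, by the normal approximation and before loss to follow-up, 84 per group at 0.025 and 113 per group at 0.05/8.

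**The case against.** A reader might infer that the plan commits itself to at least eight primary tests at 5%, any one of which proves superiority. The text does not say that. The 5% per test is carried over from the sample-size paragraph. The any-one-suffices rule is inferred from the lack of a decision rule; if every test had to succeed there would be no inflation, although the power would then be lower than stated. Eight is not a floor, because a MANCOVA can test FIM and SF-36 jointly, leaving four tests. The Introduction also poses separate sub-questions for quality of life and functional status. With one family per outcome, four visits each, the same simulation gives 11-16% at between-visit correlation 0.5-0.8. Counting two SF-36 summary scores to reach twelve tests would add something the article does not mention. All of this stands, and it is why the size is given as a range.

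It can also be said that multiplicity control is commonly left to an analysis plan, and that the article already leans towards T1: it powers T1 and discards patients whose T1 is missing, while imputing later visits. This carries less weight. Silence on adjustment would be no finding, but the point here is a conflict between two things the article does state. An unseen plan that split alpha would not be supported by 71 per group. One that made FIM at T1 the sole deciding test would have to override two equal primary outcomes and the rule covering T1-T4.

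Two nearby items do not strengthen the point. Under Primary outcome measures the article says "the primary outcome measures are FIM, measuring quality of life and SF-36, measuring functional health status", which reverses the abstract and Table 2. This is a clerical slip with no effect on error rates. The use of a motor FIM benchmark when the outcome is called FIM is a separate sample-size matter. Separate tests at each visit are also valid visit by visit, so a longitudinal model is a preference and not a necessity.

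**Conclusion.** The point holds as a mismatch between the stated tests and the stated sample size. Two unranked primary outcomes are compared at each of four visits, only FIM at T1 is powered, and nothing says which result decides the general hypothesis.

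If every test is made at 5% and any one suffices, the family-wise error lies between about 10% and 34%, or roughly two to seven times nominal. The upper end is eight independent tests; the lower end is four omnibus tests with between-visit correlation 0.9. This range depends on the two inferred rules and on correlations the article does not give, so no single value in it should be quoted as a property of the plan. The loss of power under split alpha depends on none of the correlations and follows from the article's own figures.

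**What to change.** In Statistical analyses, name FIM at T1 as the first confirmatory test at two-sided 5%, specifying the same FIM score as was used for the sample size. Test one named SF-36 score at T1, also at two-sided 5%, only if the first test is significant. Report T2-T4 as secondary with confidence intervals, preferably from one longitudinal model per outcome; that last element is optional for error control. State the order before any outcome comparison between services is made.

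The fixed sequence holds the family-wise error of the two confirmatory tests at 5%, keeps the stated 80% power for FIM and needs no more patients. It is more than an edit of wording, because it changes the standing of some results: the SF-36 claim becomes conditional on FIM, and T2-T4 are no longer confirmatory. The reversed description of the two instruments can be corrected in the same revision.

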3) an earlier start of both specific physical and psychosocial treatment provided by a multidisciplinary team;

4) early individual goal setting;

5) early start of psychological and social counselling;

6) an integrated co-ordination of treatment between the trauma surgeon and the rehabilitation physician, and

7) a shorter stay in a trauma rehabilitation unit

may be more (cost-) effective. Such SFTRS approach may lead to less secondary complications associated with immobilisation, which would negatively influence recovery and quality of life. Early personalised goal setting and early treatment of depression are known to positively affect outcome. SFTRS may lead to faster reintegration into society. Early return to work and active support from the multidisciplinary rehabilitation team will lead to a more stable social network, and the patient becoming less reliant on professional care in the long term. Also, the SFTRS may reduce the length of stay of multi-trauma patients in a hospital. Furthermore, earlier rehabilitation treatment in a specialised rehabilitation unit may also reduce the length of stay in the rehabilitation clinic, thus reducing costs of hospital/clinic consumption. At this moment it is not possible to make a precise calculation of these savings. Since earlier discharge also means that patients take part in society and work earlier, costs related to production losses and patient & family costs are expected to be lower.

The main objective of this study is to examine the effectiveness, costs and cost-effectiveness of an integrated care service for multi-trauma patients, called 'Supported Fast track multi-Trauma Rehabilitation Service' or SFTRS.

The general research question is:

Which of 2 rehabilitation services, i.e. 'Conventional multi-Trauma Care Service' (CTCS) or 'Supported Fast track multi-Trauma Rehabilitation Service' (SFTRS), is most (cost-) effective from a societal point of view?

Sub-questions are:

- What are the effects of the SFTRS on generic quality of life in multi-trauma patients as compared to the CTCS?

- What are the effects of the SFTRS on functional health status as compared to the CTCS?

- What are the costs to health care and to society of the SFTRS as compared to the CTCS?

- What is the cost-effectiveness of the SFTRS as compared to the CTCS?

The general hypothesis of this study is that SFTRS is more (cost-) effective than CTCS.

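### The 71 per group and its 80% power belong to a univariate comparison of FIM at T1, but the only between-service test named is a MANCOVA, whose power the protocol does not determine

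*Protocol article*

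**What the plan says.** **Sample size (Protocol article, Methods, Population).** The starting point is an external study said to "report an improvement in motor FIM score of 30.2 in a small group of bilateral lower limb multi trauma patients". The target is set as follows: "In order to detect a difference of 15% of such improvement in FIM score between SFTRS and CTCS at T1". The remaining inputs are "assuming a two-sided significance level of 0.05, a power of 80" per cent, and "a common standard deviation (sd) of 9.5". The result is "71 persons per group are needed". Then: "Taking into account a 15% loss to follow-up, the required sample size is 82 persons per group (164 persons in total".

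**Test (Methods, Statistical analyses).** For each of the data sets from T1 to T4, "differences in outcome variable between the 2 services will be tested using multiple MANCOVA's, entering various indicators of case mix as co-variates". Five covariates are listed: age, gender, ISS, number of complications and pre-trauma psychosocial status. The section does not say which outcomes enter which MANCOVA. It also provides that patients without a T0 or T1 measurement are discarded and replaced until 82 per group is reached.

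**Questions (Introduction).** Functional health status has its own sub-question: "What are the effects of the SFTRS on functional health status as compared to the CTCS". Generic quality of life has a separate one. Table 2 lists two primary outcomes, SF-36 and FIM.

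**The concern.** The sample-size paragraph uses one mean difference and one standard deviation. It uses no second outcome, no correlation between outcomes and no number of dependent variables. A MANCOVA needs all three before its power can be stated. It tests a single hypothesis over a vector of outcomes and spends one numerator degree of freedom on each outcome entered. The same FIM difference therefore gives a different power, which may be lower or higher depending on what the other outcomes do.

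There is also a question of interpretation. The omnibus test rejects when any combination of the outcomes differs, including one better and another worse. Taken alone, it gives no FIM difference with a confidence interval and does not separate FIM from SF-36, although the sub-questions ask about each.

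The point concerns the form of the test at one visit, T1. It is not about the number of tests across visits.

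**Working it through.** **Inputs from the document.** Reference improvement 30.2, fraction 15%, SD 9.5, two-sided alpha 0.05, power 80%, 71 per group evaluable, 82 per group after inflation, five covariates.

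**Inputs not in the document, assumed here.** Number of outcomes per MANCOVA, their correlation, the service effect on the second outcome, and the outcome variance explained by the covariates. The covariates are taken as balanced between the centres.

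**Step 1: reproduce the 71.**
- Difference = 0.15 × 30.2 = 4.53; d = 4.53 / 9.5 = 0.477.
- Normal approximation: n = 2 × (1.960 + 0.842)² / 0.477² = 69.04, rounded up to 70.
- Exact two-sample t-test (noncentral t, 2n − 2 degrees of freedom, noncentrality d × √(n/2)): power 79.99% at 70 and 80.6% at 71.

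So 71 is exactly the smallest n per group for a two-sample t-test on FIM alone.

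**Step 2: a single-outcome ANCOVA on FIM.** With five covariates that explain no variance, power is 80.5% at 71 per group and 85.9% at 82. The stated sample size fits this test.

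**Step 3: a two-outcome MANCOVA.** For two groups and p outcomes, the F statistic has p and 2n − 2 − 5 − p + 1 degrees of freedom and noncentrality (n/2) × D², where D² is the squared Mahalanobis distance between the services. With two outcomes, effects d and e, and correlation r:

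D² = (d² + e² − 2rde) / (1 − r²).

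The smallest possible value is D² = d² = 0.227, reached when the second outcome adds no separation.
- At 71 per group: noncentrality 35.5 × 0.2274 = 8.07 on 2 and 134 degrees of freedom; power 71%.
- At 82 per group: noncentrality 41 × 0.2274 = 9.32 on 2 and 156 degrees of freedom; power 78%.

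The 82 is relevant at T1 because of the replacement rule.

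**Step 4: vary the assumptions (two outcomes, 71 per group, covariates explaining nothing).**

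| Effect on second outcome | r = 0 | r = 0.3 | r = 0.5 | r = 0.7 |
|---|---|---|---|---|
| 0 | 71% | 75% | 84% | 95% |
| 0.2 SD | 78% | 72% | 72% | 78% |
| 0.3 SD | 85% | 76% | 72% | 72% |
| 0.477 SD | 95% | 89% | 84% | 78% |

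Power runs from 71% to 95%, on both sides of 80%.

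**Step 5: let the covariates explain variance.** In the minimum case of step 3, replace d² by d² / (1 − R²). At 71 per group, R² of about 0.19 brings power back to 80%. At 82 per group, R² = 0.10 gives 82%. Covariate imbalance between the two centres would work the other way: at 71 per group with R² = 0, if the covariates explain 10% of the variation in service membership, two-outcome power falls from 71% to 66%.

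**Step 6: larger vectors, hypothetical only.** The document defines no five- or nine-variable vector. At 71 per group the minimum would be 55% for five variables and 43% for nine. If all outcomes shift by 0.477 SD with a common correlation of 0.3, power would be 92% and 90%. These figures show how wide the range is and say nothing about the trial's actual power.

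**The case against.** **The MANCOVA may be a loose name.** The analysis sentence puts the outcome variable in the singular, so separate covariate-adjusted analyses per outcome may be what is meant. On that reading 71 per group fits FIM. This is a fair reading, but then the method is misnamed and needs the same correction.

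**A reader might infer that the trial is underpowered.** The documents do not support that. The vector is not defined, and the protocol itself hypothesises that quality of life improves as well, which can raise the power. The replacement rule plans 82 per group at T1, where the two-outcome minimum is 78%. Covariates chosen because case mix affects outcome may recover the rest.

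**A reader might infer that the plan cannot isolate a FIM effect.** That is true of the omnibus statistic alone. Univariate tests customarily follow a MANCOVA and may be set out in a fuller document that is not shown, so their absence from an article is no finding. The cost-effectiveness analysis also plans an incremental FIM result. But if follow-up tests are made only after the omnibus test rejects, their power is again not simply the stated 80%.

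**Sizing on one outcome with a simple formula is common practice.** It is, and the paragraph ties its 80% to FIM at T1. What remains is that the analysis section names a different kind of test and no test to which that 80% applies.

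**Conclusion.** The point holds as a mismatch between the sample-size basis and the named test. The 71 per group and the 80% are those of a univariate FIM comparison at T1, confirmed exactly. If two or more outcomes share a MANCOVA, its power cannot be determined from the document. The two-outcome minimum, with covariates that explain no variance and are balanced between the centres, is 71% at 71 per group and 78% at 82. Power exceeds 80% if, for example, the second outcome shifts as much as FIM with low to moderate correlation, or if the covariates explain enough outcome variance. The supportable statement is that the power is unspecified, not that it is too low. Separately, the omnibus statistic on its own does not answer the two sub-questions, although customary univariate follow-up would. The plan should be changed because a better-matched analysis is available at almost no cost.

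**What to change.** In Statistical analyses, name a covariate-adjusted ANCOVA of FIM at T1 as the primary test, state that the sample size and its 80% power refer to this comparison only, and report the adjusted difference with its 95% confidence interval. Give SF-36 its own ANCOVA, so that the quality-of-life sub-question has its own answer. If a MANCOVA is kept, list the outcomes that enter it and label it supportive.

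The cost is a change of analysis wording, with no new data and no extra patients. The small downside is that a single global test across outcomes is no longer the main result.
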